### Interventions

#### Description of the study nets

The nets are blue, rectangular, and identical sizes (1.8 m long, 1.6 m wide, and 1.8 m high); however, the Royal Guard® textile is different from the other two nets (details below). The three net brands are all WHO pre-qualified vector control products [31].

Intervention 1: Interceptor® G2 (BASF Corporation) is a mixture LLIN made of polyester netting (100 deniers) coated with a wash-resistant formulation of 200 mg/m^2^ chlorfenapyr and 100 mg/m^2^ alpha-cypermethrin. Chlorfenapyr is a member of the pyrrole class of insecticides [32] and disrupts cellular respiration and oxidative phosphorylation in mitochondria and due to this unique mode of action is toxic to mosquitoes that are resistant to standard neurotoxic insecticides like pyrethroids [33]. No record of cross-resistance to chlorfenapyr has been reported up to now.

Intervention 2: Royal Guard® (Disease Control Technologies, LLC) is a mixture LLIN made of polyethylene (120 deniers) incorporating 225 mg/m^2^ pyriproxyfen and 261 mg/m^2^ alpha-cypermethrin. Pyriproxyfen is a multiple acting compound (known as a juvenile hormone analogue) with insecticidal and sterilising effects on females which is known to disrupt reproduction and fertility of eggs [34].

Control: Interceptor® LLIN (BASF Corporation) is a pyrethroid-treated LLIN with alpha-cypermethrin (coated onto filaments) at a target dose of 200 mg/m^2^ of polyester fabric (100 deniers). Interceptor was chosen as a direct comparison to Interceptor G2 and Royal Guard as all three nets are impregnated with alpha-cypermethrin pyrethroid (albeit at different concentrations) and because some pyrethroid resistance mechanisms involving CYP6 genes are specific to type I (permethrin) or type II (alpha-cypermethrin) pyrethroids [35].

#### Intervention description

Nets will be distributed with the support of the National Malaria Control Programme (NMCP). All households in the study area will receive one net for every two people. The census listing will be used to facilitate net distribution at a central location in each hamlet. To reach a minimum of 85% access following the distribution and a minimum of 75% usage, information, education, and communication (IEC) activities will be conducted before, during, and after LLIN distribution to increase usage in the study area, including instructions on when and how to wash the nets. A door to door hang-up campaign will take place after the distribution and depending on net usage rates, subsequent hang-up campaigns will be organized to increase net usage. Throughout the study, community health workers will be utilized to encourage continuous net use in the study population. Hamlet and religious leaders will be also involved in the sensitization campaigns for net usage.

The coverage achieved in each cluster will be evaluated through a post-intervention coverage survey one month after distribution. Net coverage and usage will also be assessed during cohort visits and cross-sectional surveys. Three indicators will be used: “proportion of households with at least one ITN for every 2 people”, “proportion of household members with enough ITNs to sleep under (population access)” and “proportion of residents reporting using an ITN last night” [36, 37].

### Outcomes

The *primary outcome* is malaria case incidence in children aged 6 months to 10 years (Table 1) over 24 months. A malaria case is defined as an infra-rouge frontal temperature above 37.5 °C or history of a fever in the last 48 h and a positive rapid diagnostic test (RDT).

**Table 1 Tab1:** Study outcomes, measurements, and process of collection

Outcome	Measurement	Collection
**Epidemiological outcomes**		
Malaria case incidence	Rapid diagnostic test taken when temperature ≥ 37.5 °C and/or history of fever for the past 48 h	Active case detection: cohort follow-up
Malaria infection prevalence	Rapid diagnostic test whatever the presence of malaria signs	Cross-sectional survey
Moderate to severe anaemia	Haemoglobin (measured by Haemocue), defined as < 10 g/dL and < 8 g/dL, respectively.	Active case detection: cohort follow-up Cross-sectional survey
Temperature	Digital infra-red ear thermometer Temperature and history of fever	Active case detection: cohort follow-up Cross-sectional survey
**Entomological outcomes**		
Indoor and outdoor *Anopheles* biting density	Human landing catch	Entomology monitoring
Mosquito sporozoite rate	Standard CSP-ELISA uses to estimate the EIR. The positive sample will be confirmed with a second ELISA using a heating technique	Entomology monitoring
*Anopheles* species identification	*An. gambiae*, *An. coluzzii* and *An. funestus* Taq Man Real time PCR	Entomology monitoring Sentinel site and resistance test
Resistance intensity	WHO cylinder assay, collection of adult *Anopheles* resting indoor	Entomology monitoring
Frequency of Vgsc mutation	Taq Man PCR	Entomology monitoring
Identification and intensity of overexpressed CYP6 genes	Screening for CYP6 genes by using Microarrays Reverse-transcription quantitative PCR (RT-qPCR) using for confirming and monitoring the expression of the cytochrome identified	Resistance activity, unfed 3 days old adult *Anopheles* from larval collection

*Abbreviations*: *EIR* Entomological inoculation rate

#### Secondary outcomes are

Malaria infection prevalence in the study population at 6 and 18 months post bed net distribution,Prevalence of moderate to severe anaemia in children under 5 years old at 6 and 18 months post bed net distribution,EIR, as a measure for malaria transmission rate in the primary vector species.

*Other outcomes* are:
Mosquito density and survivorship, mosquito resting behaviour, species composition, ovary development, and fecundity.Frequency and intensity of phenotypic and genotypic resistance to pyrethroid, chlorfenapyr, and pyriproxyfen insecticides.Prevalence of elevated cytochromeP450s and other metabolic enzymes associated with pyrethroid resistance [38].

### Sample size

Sample size calculation for the primary outcome (malaria case incidence in children aged between 6 months and 10 years) was based on the method of Hayes and Bennett [39]. Based on passive data collected in 2018 by the NMCP in the study area, the mean number of malaria episodes per child per year in the reference arm was assumed to be 1. We assumed a between-cluster coefficient variation of 0.3 and that dual-AI LLINs will reduce malaria case incidence by 30% (i.e. to 0.7 cases per child per year). With a follow-up of 2 years, to detect this effect size with 80% power would require following 20 children and 5 additional children to account for the loss of follow-up (25 in total) in 20 clusters in each of the three arms. This sample size calculation includes adjustment for multiple testing (allowing for the 3 arms) using a Bonferroni-corrected two-sided alpha of 1.67%. This results in a total of 60 clusters required for the trial and a cohort of 1500 children.

For the cross-sectional surveys, it was assumed that malaria prevalence in the reference arm is 40%, with a coefficient of variation between clusters of 0.3. With 70 individuals per cluster and 20 clusters per arm, the study will have 80% power to detect a relative 30% lower prevalence (prevalence ratio 0.70) between each intervention arm to standard LLIN using a Bonferroni-corrected two-sided alpha of 1.67% to account for multiple comparisons.

To achieve adequate participant enrolment to reach the target sample size, enhanced community sensitization activities will be conducted before and during each activity in the community with the support of hamlet leaders and community health workers.

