### Trial status

Baseline surveys are completed, and the cohort recruitment is currently running. Due to the COVID-19 pandemic and the cases confirmed in Benin, the recruitment of cohort children has been postponed from April to July 2020. Entomological collection using human landing catches were also suspended and resumed at the end of June. Laboratory work and hut trial work continued as normal. This delay has led to the loss of 3 months of data collection; therefore, the sample size has been modified accordingly. With a follow-up of 21 months, 30 children instead of 25 per cluster would be required for detecting the impact of the study nets. For mosquito collection, each cluster will be visited seven times over the 21 months follow-up period. The amendments have been submitted to the different ethics committee. All staff is using appropriate protective equipment and hand sanitation measures.

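### At the stated two-sided alpha of 1.67%, the primary sample-size inputs need 22 clusters per arm; the planned 20 give about 76% power, not 80%

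*Protocol article*

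**What the plan says.** The Sample size section of the protocol article says that the primary calculation "was based on the method of Hayes and Bennett". It gives every input:

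- Control rate: "the mean number of malaria episodes per child per year in the reference arm was assumed to be 1".
- Effect: "dual-AI LLINs will reduce malaria case incidence by 30% (i.e. to 0.7 cases per child per year").
- Clustering: "We assumed a between-cluster coefficient variation of 0.3".
- Follow-up of two years. On cohort size, "to detect this effect size with 80% power would require following 20 children and 5 additional children", so 25 enrolled and 20 retained per cluster, with 20 clusters in each of three arms.
- Significance level: the calculation is described as "using a Bonferroni-corrected two-sided alpha of 1.67%. This results in a total of 60 clusters".

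Statistical methods, Primary outcome, describes two comparisons, each dual-ingredient net against the reference net. It promises a Bonferroni adjustment but prints no number.

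Trial status then reports a change made because of the pandemic: "With a follow-up of 21 months, 30 children instead of 25 per cluster would be required for detecting the impact of the study nets". It gives no new number of clusters, loss rate, power or alpha.

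**The concern.** The method and all its inputs are printed, so the stated result should be reproducible from the text. It is not: at 1.67% the formula asks for more than 20 clusters. Either the power or the alpha is misstated.

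This matters beyond bookkeeping. The 1.67% in the Sample size section is the only numeric threshold in the article. If the analysis applies it, a non-significant net comparison will be read against 80% power that the design does not have. If the analysis applies 2.5%, the 80% holds, but the printed threshold is wrong. The Background and Discussion say that the results go to WHO review for a policy recommendation, and those readers need an alpha and a power that belong to the same design.

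**Working it through.** **Formula.** Hayes and Bennett, unmatched clusters, event rates:

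c = 1 + (z₁₋α/₂ + z₁₋β)² × V, where V = [(λ₀ + λ₁)/y + k²(λ₀² + λ₁²)] / (λ₀ − λ₁)²

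Power for a given c is Φ(√((c − 1)/V) − z₁₋α/₂).

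**Inputs, all from the Sample size section.** λ₀ = 1.0; λ₁ = 0.7; k = 0.3; y = 20 retained children × 2 years = 40 child-years per cluster; power 80% (z = 0.842).

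**Variance term.**
- Within clusters: 1.7/40 = 0.0425
- Between clusters: 0.09 × (1 + 0.49) = 0.1341
- V = (0.0425 + 0.1341)/0.09 = 1.962

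**Reproducing the plan's 20 clusters.** At two-sided 2.5% (0.05/2), (2.241 + 0.842)² = 9.505 and c = 1 + 9.505 × 1.962 = 19.65, which rounds up to 20. Power at 20 clusters is Φ(√(19/1.962) − 2.241) = Φ(0.870) = 80.8%.

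**The same calculation at the stated alpha.** At two-sided 1.67% (0.05/3), (2.394 + 0.842)² = 10.47 and c = 1 + 10.47 × 1.962 = 21.54, so 22 clusters per arm and 66 in total. Power at 20 clusters is Φ(3.112 − 2.394) = Φ(0.718) = 76.4%. Solving for λ₁ at 80% power with 20 clusters gives 0.689, a reduction of 31.1%.

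**Other versions at two-sided 1.67%, 20 clusters per arm**

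| Version | Clusters needed | Power at 20 |
|---|---|---|
| Named formula, 40 child-years | 21.54 → 22 | 76.4% |
| Without the +1 | 20.54 → 21 | 78.8% |
| t-test on 38 df | – | 75.1% |
| No loss at all (25 × 2 = 50 child-years), with the +1 | 20.55 → 21 | 78.7% |
| No loss and no +1 | 19.55 → 20 | 81.0% |
| Log-rate scale, with the +1 | – | 78.1% |
| Log-rate scale, without the +1 | – | 80.4% |

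**Amended cohort (21 months = 1.75 years, 30 enrolled).** Trial status gives no loss rate, so a range is shown. It also reports no change in the number of clusters, so 20 per arm is assumed. All rows use the named formula.

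| Retained children | Child-years per cluster | Power at 1.67% | Power at 2.5% |
|---|---|---|---|
| 24 (the original 20% loss) | 42 | 76.9% (c = 21.31 → 22) | 81.3% |
| 25 (the original allowance of 5) | 43.75 | 77.3% | 81.7% |
| 30 (no loss) | 52.5 | 79.1% | 83.2% |

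Extra children help little because the between-cluster part of the variance (0.1341) is about three times the within-cluster part (0.0425). Keeping 20 clusters at 1.67% would take 1.7/(19 × 0.09/10.47 − 0.1341) ≈ 58 child-years per cluster. That is about 30 retained children over two years, or 38 enrolled at the plan's 20% loss.

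**A second calculation with the same pattern.** The prevalence calculation in the same section uses 40% versus 28%, k = 0.3 and 70 people per cluster. It names no method; assuming the Hayes and Bennett formula for proportions, it needs 21.2 clusters at 1.67% (77.2% power at 20) and 19.3 at 2.5% (81.5%).

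**The case against.** The strongest reply is that alpha, not power, is the misprinted number. The analysis section describes two comparisons, Bonferroni for two is 2.5%, and at 2.5% the design gives the stated power with exactly 20 clusters. On that reading the trial has its 80% and only one figure needs correcting. This is plausible, and the prevalence calculation supports it. It remains an inference, since the article twice states 1.67% and never 2.5%. It also explains the contradiction without removing it.

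The other replies narrow the gap:

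- **Precision of the inputs.** k = 0.3 is an assumption given to one decimal place. At k = 0.285, which still rounds to 0.3, 20 clusters give 80% at 1.67%. True, but 0.3 is the value the plan says it used.
- **Covariate adjustment.** The primary analysis adjusts for the restriction variables. If that removed about 10% of the between-cluster variance (k² from 0.090 to 0.081), power would reach 80%. The article claims no such gain in its calculation and gives no figure for it.
- **Choice of variant.** The text says only that the calculation was based on the method. Dropping the +1 alone still needs 21 clusters. Among the two-sided versions above, reaching 80% at 1.67% takes a second departure: ignoring loss, which contradicts the five children added for it, or moving to a log scale.

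What stands is that the shortfall is small, that 76% depends on an unadjusted formula with rounded inputs, and that the point shares its cause with the choice of alpha and should be settled together with it.

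**Conclusion.** The concern holds. Under the named method and the printed inputs, 20 clusters per arm at two-sided 1.67% give 76.4% power, 3.6 points below the stated 80%; 22 clusters per arm would be needed. The amended cohort gives 76.9% if the 20% loss is carried over and 79.1% with no loss at all, so it does not close the gap. These figures rest on the standard unmatched formula with the +1 and on 20 retained children per cluster for the original design.

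This is a reproducible error in the primary sample-size statement. It does not bias the estimates or undermine the trial. The probable cause is that the count was worked out for two comparisons and reported with a correction for three, but the article does not show this.

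**What to change.** Settle alpha before unblinding, then make the numbers agree. There are two ways:

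1. State a two-sided alpha of 2.5% for the two primary comparisons with control, in both the Sample size section and the primary analysis. Power is then 80.8% for the original design and 81.3% for the 21-month cohort at 20% loss.
2. Keep 1.67% and report power of about 76% for the original design and about 77% as amended, or a detectable reduction of about 31% at 80% power for the original design.

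The first fits the comparisons that the analysis section describes. Under either, restate the calculation for 30 children over 21 months, with its loss rate, alpha and power, and carry that design through the primary outcome and sample-size text. Apply the same alpha to the prevalence calculation, or say why it differs.

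The cost is wording only, with no extra clusters or children. Restoring 80% at 1.67% by enlarging the trial would instead take 22 clusters per arm, or about 38 enrolled children per cluster over two years.

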#### Primary outcome

To assess whether the new dual-AI LLINs are superior to the reference LLIN, malaria case incidence in each intervention arm (Royal Guard and Interceptor G2) will be compared to malaria case incidence in the reference arm (Interceptor). To adjust for the increased risk of type I error due to multiple pairwise comparisons, the level of significance will be adjusted using the Bonferroni method. Following any treatment for malaria, a child will not be considered at risk for two weeks. Multilevel mixed models with random effects will be used to test the difference in incidence rate between each intervention and the control arm, allowing for repeated measurements on the same individual, and within-cluster correlation of responses. Survival analyses will be also used to compare time to the first infection case, adjusting for confounding factors using a Cox proportional hazards model. Multiple events will be allowed per child (with appropriate censoring to account for prophylactic protection following treatment and absence during follow-up visits).

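### The sample-size alpha is divided by three arms (1.67%) although only two confirmatory comparisons are planned; at 1.67% the stated 80% power is missed by a few points, and the analysis section gives no divisor

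*Protocol article*

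**What the plan says.** All references are to the Protocol article.

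- **Sample size, incidence.** The level and the reason for it are given in one sentence: "This sample size calculation includes adjustment for multiple testing (allowing for the 3 arms) using a Bonferroni-corrected two-sided alpha of 1.67" per cent. At that level the section claims 80% power with 20 clusters per arm and 20 retained children per cluster (25 enrolled) over two years.
- **Sample size, prevalence.** The same level is used for the cross-sectional surveys, again for contrasts "between each intervention arm to standard LLIN using a Bonferroni-corrected two-sided alpha of 1.67" per cent, with 80% power claimed.
- **Statistical methods, Primary outcome.** Two contrasts are named: "malaria case incidence in each intervention arm (Royal Guard and Interceptor G2) will be compared to malaria case incidence in the reference arm (Interceptor"). On multiplicity the section says only that "the level of significance will be adjusted using the Bonferroni method". It gives neither a divisor nor a level.
- **Study objectives.** The primary objective and the infection and anaemia objective set the dual-ingredient nets against the pyrethroid-only net. No confirmatory comparison of Royal Guard with Interceptor G2 is stated.
- **Trial status.** The cohort is changed to 30 children per cluster followed for 21 months. No alpha is given for that revised calculation.

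**The concern.** Three arms allow three pairs, but only two of those pairs are declared for the outcomes powered at 1.67%. The divisor therefore does not fit the stated hypotheses. Two tests at 1.67% use at most 3.33 of the 5 percentage points available, so a third of the allowance is unused.

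Two things are at stake. First, the design claims 80% power at an alpha at which the stated numbers do not appear to deliver it. Second, because the analysis section leaves the divisor open, the 1.67% could become the decision threshold by default. A superiority claim would then face a stricter test than two comparisons require, in a trial meant to inform a WHO recommendation.

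**Working it through.** **Inputs (Sample size section).** Rates 1.0 and 0.7 per child-year; between-cluster coefficient of variation k = 0.3; 20 clusters per arm; 20 retained children × 2 years = 40 child-years per cluster. Prevalence: 40% and 0.70 × 40% = 28%, 70 people per cluster, k = 0.3. Amended cohort (Trial status): 30 × 1.75 years = 52.5 child-years with no losses. If 20% are lost, as in the initial allowance (5 of 25), 24 remain and give 42 child-years; applying that loss rate here is my assumption.

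**Formula.** The article names the method of Hayes and Bennett but does not print the formula. The standard form for rates is

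c = 1 + (z_α/2 + z_β)² × [(r0 + r1)/y + k²(r0² + r1²)] / (r0 − r1)²,

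and for proportions (r0 + r1)/y is replaced by [p0(1 − p0) + p1(1 − p1)]/m. Results without the leading 1 are shown as a sensitivity check.

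**Alpha.** 5%/3 = 1.67%; 5%/2 = 2.5%. Two tests at 1.67% give a family-wise error of at most 3.33%. With the shared control (correlation 0.5 for equal arms) it is about 3.1%, against 4.6% for two tests at 2.5%. Both are under 5%.

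**The article's own figure, incidence.** Bracket: 1.7/40 + 0.09 × 1.49 = 0.0425 + 0.1341 = 0.1766. Divided by 0.3² = 0.09, this is 1.962.

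- At 1.67%: (2.394 + 0.842)² = 10.47, so c = 1 + 10.47 × 1.962 = 21.54, i.e. 22 clusters per arm. The stated 20 is not reproduced.
- At 2.5%: (2.241 + 0.842)² = 9.505, so c = 1 + 9.505 × 1.962 = 19.65, i.e. 20 clusters per arm.

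Power with 20 clusters is Φ(√(19/1.962) − z_α/2), and √(19/1.962) = 3.112. At 1.67%: Φ(3.112 − 2.394) = 76.4%. At 2.5%: Φ(3.112 − 2.241) = 80.8%.

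**Prevalence.** Bracket: 0.4416/70 + 0.09 × 0.2384 = 0.00631 + 0.02146 = 0.02776. Divided by 0.12² = 0.0144, this is 1.928. At 1.67%, c = 21.19 (22 clusters) and power is 77.2%. At 2.5%, c = 19.33 (20 clusters) and power is 81.5%.

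**Power with 20 clusters per arm:**

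| Scenario | 1.67% | 1.67%, no +1 | 2.5% | 2.5%, no +1 |
|---|---|---|---|---|
| Incidence, 20 retained, 2 years | 76.4% | 78.8% | 80.8% | 82.9% |
| Incidence, all 25 retained, 2 years | 78.7% | 81.0% | 82.8% | 84.9% |
| Prevalence, 70 per cluster | 77.2% | 79.6% | 81.5% | 83.6% |
| Amended cohort, 30 retained, 21 months | 79.1% | 81.4% | 83.2% | 85.2% |
| Amended cohort, 24 retained, 21 months | 76.9% | 79.3% | 81.3% | 83.4% |

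A t-test on cluster rates with 38 degrees of freedom (20 retained, 2 years) gives 75.1% at 1.67% and 80.1% at 2.5%.

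**Children needed with 20 clusters per arm, 2 years.** At 1.67%: 29.1 retained per cluster (22.5 without the +1). At 2.5%: 18.6. The stated figure is 20.

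**The case against.** Four points can fairly be made for the plan.

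1. **The error is on the safe side.** Dividing by three cannot inflate type I error, bias an estimate or undermine a positive result. This stands, and it limits the weight of the point.
2. **The analysis threshold is not fixed at 1.67%.** A reader might infer that a net with a p-value between 0.0167 and 0.025 will be declared not superior. The document does not support that. The figure appears only under Sample size. The analysis section names two contrasts and then Bonferroni, which could equally be read as 2.5%, and an analysis plan that is not shown may settle it. What stands is narrower: the one published level does not fit the two contrasts, and the analysis section does not correct it.
3. **The shortfall depends on convention.** Without the +1 term, incidence and prevalence power at 1.67% come within about 1 point of 80%. With no losses as well, incidence passes it (81.0%, or 81.4% for the amended cohort). This stands as a reason to report a range. But the article plans on 20 retained children, and every variant on that basis is below 80% at 1.67% and above it at 2.5%.
4. **The divisor alone does not explain the missed power.** A correct calculation at 1.67% would have asked for more clusters or children. A reader might infer that the size was in fact computed at 2.5%, since 20 clusters fits that level; the article does not show its working, so this cannot be established.

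**Conclusion.** The point holds as an inconsistency with a modest cost. The divisor is the number of arms, while the article declares two confirmatory comparisons, for which the Bonferroni level is 2.5%. Type I error is protected, with family-wise error at most 3.3%. The price is about 4 points of power (4.4 for incidence, 4.3 for prevalence). Separately, the 80% claimed at 1.67% is not reproduced by the named method on the article's own inputs, and the amended cohort does not restore it under that formula.

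This rests on the standard Hayes-Bennett form, the article's rates, prevalence and k, and, for the lower amended figure, an assumed 20% loss. It also rests on there being no confirmatory comparison of the two new nets; if one were declared, a divisor of three would be right and only the power statement would need correcting. The point should be fixed, but it does not threaten the validity of the trial.

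**What to change.** Choose one of two consistent positions, by documented amendment before unblinding.

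- **Two comparisons.** State in both Sample size and Statistical methods (Primary outcome) that each dual-ingredient net is tested against Interceptor at two-sided 2.5%. Restate the 21-month, 30-child calculation in Trial status with its alpha, assumed losses and resulting power.
- **Three comparisons.** Keep 1.67%, name Royal Guard against Interceptor G2 as the third confirmatory test, write the divisor into the analysis section, and restate power for the contrasts with control as about 76% to 79% by the named formula. Restoring 80% instead would need 22 clusters per arm on the initial cohort assumptions, which is 66 in total against the 60 already randomised.

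Holm or Dunnett across the two comparisons would be an optional gain; Bonferroni at the right divisor is valid. The first option costs a few sentences and no clusters or children. It does relax a published level after recruitment has begun, so the amendment should give the reason and record that it was made blind to arm-level results.
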